#### 7.11.2 Oral Steroid

Participants will be asked at their 6 week follow up visit whether they took the full course of treatment and this will be recorded on the relevant CRF.

#### 7.11.3 Intratympanic Injection Steroid

Adherence will be documented in the relevant CRFs using information available in the medical notes.

#### 7.11.4 Pure tone audiogram and speech testing

Adherence should be documented in the relevant CRFs using information available in the medical notes.

### 7.12 Accountability

Participants will receive their medication as per usual pharmacy practice at trial sites. As participants are receiving standard care, no additional monitoring is required.

## 8 OUTCOME MEASURES

### 8.1 Internal Pilot Outcome

The success of the 9-month internal pilot study will be based upon the recruitment rate, adherence to the treatment allocation and dropout rate. At 9 months, it is anticipated that the trial will have recruited 81 participants from at least 36 centres. For the trial to continue pre-defined stop-go criteria must be met. A traffic light system has been designed to determine continuation to the full trial:

**Green:** Recruitment rate  $\geq 100\%$ , adherence rate  $\geq 90\%$ , and dropout rate  $< 5\%$ . If all three criteria are met, the trial will continue with the protocol unchanged.

**Amber:** Recruitment rate 70-99%, adherence rate 70-89%, or dropout rate 5-10%. If one or more of the criteria are met, the trial will be reviewed to determine the changes (if any) that could be made to improve whichever criteria are not at the green level.

**Red:** Recruitment rate  $< 70\%$ , adherence rate  $< 70\%$ , or dropout rate  $> 10\%$ . If one or more of these criteria are met, this will be discussed with the Trial Steering Committee (TSC) and funder regarding feasibility of the trial continuing.

**Table 1:** Internal pilot progression criteria

|                         | Red  | Amber   | Green |
|-------------------------|------|---------|-------|
| Recruitment threshold   | <70% | 70%-99% | ≥100% |
| Adherence threshold     | <70% | 70%-89% | ≥90%  |
| Drop-out rate threshold | >10% | 5-10%   | <5%   |

## 8.2 Main Trial Outcomes

### 8.2.1 Primary Outcome

- **The absolute improvement in pure tone audiogram average at 12 weeks** following randomisation (calculated at 0.5, 1.0, 2.0, 4.0 kHz). Conducted by an audiologist blinded to the treatment allocation.

### 8.2.2 Secondary Outcomes

All secondary outcomes will be measured at 6 and 12 weeks following randomisation, except where stated.

#### Functional hearing

- **Hearing related to speech: using The Speech, Spatial and Qualities of hearing scale (SSQ).** SSQ is a validated measure, in the form of a short questionnaire, known to provide a good representation of the functional relationship with speech in everyday life and has been used to assess the disability of unilateral hearing loss seen in ISSNHL (19), providing disability scores associated with different aspects of hearing. **(Key secondary outcome)**
- **The absolute improvement in pure tone audiogram average at 6 weeks** following randomisation (calculated at 0.5, 1.0, 2.0, 4.0 kHz). Conducted by an audiologist blinded to the treatment allocation.
- **Actual hearing thresholds** measured by pure tone audiogram average following treatment initiation (calculated at 0.5, 1.0, 2.0, 4.0 kHz).
- **High frequency hearing threshold** measured by the absolute improvement in pure tone audiogram average across 4.0, 6.0 and 8.0 kHz.
- **Recovery of speech perception: using Arthur Boothroyd (AB) word lists scored by phoneme** (19). This speech testing will be carried out by an audiologist blinded to the treatment allocation. This measure is the most widely used in the UK and has a long history of routine use as an assessment tool for single sided hearing loss. Formal training will be provided to the audiologists. Calibration check and test setup will be provided at the training session. Continuing support can be provided throughout the trial where necessary.
- **Extent of hearing recovery: using an established classification of recovery** (complete/partial/none) based on pure tone audiogram and speech perception (1), shown in Table 2.

- 
- **Time to hearing recovery: using online digits-in-noise and pure tone tests (*Optional and recommended weekly where done*)**. Software has been developed for the trial by the HearX team, and will be iFramed on the trial website. Anonymised data entered by the participant is submitted from the client-side browser to HearX servers to store the tests. No data leaves the HearX servers except for API/csv download directly to BCTU. Weekly home testing of hearing will be encouraged in all groups. Regular testing will allow comparison of results with the pre-injection pure tone audiogram in the two intratympanic injection trial arms, and the 6 and 12 week assessments. The paired home and clinic test data will assist in validating the home tests, and provide added data on early hearing recovery in the oral steroid only group. Home testing is strongly supported by our ISSNHL PPI group and may provide valuable information for future trials of therapeutics.

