## 5.4 Additional consent

The ICF contains optional additional statements for the participant to:

- Agree that information collected about them during the study may be used to support other related research in the future, and may be shared anonymously with other researchers.

- 
- Agree to share their contact details with the STARFISH team, and to be contacted by them for up to 5 years after the trial, regarding their participation in the trial, further data collection, and to receive a summary of the trial results.
  - Agree that information held and maintained by NHS Digital and other central UK NHS bodies may be used to help contact them or provide information about their health status and medical history after the trial has ended, and agree to share their NHS number for this purpose. This will allow investigators (subject to additional funding and ethical approval) to assess longer-term impact and health service usage data without needing further contact with the trial participants.
  - Agree to use online hearing tests provided by a private company, HearX (full details are provided in section 8.3).
  - 
  - Agree to share the results of their hearing tests, but not their name, with HearX for them to use to develop a new at-home hearing test.

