### 8.3.4 Online hearing tests

Bespoke software has been developed for the trial by the HearX Group to allow regular interval testing to chart the recovery of hearing. This will be hosted on the trial website, and will allow participants to self-test their hearing online at home. It will be recommended that participants complete the online tests weekly for the 12 week follow up period, however this part of the trial will be optional. Participants without internet access or the required skills, or those who prefer not to test at home will still be able to participate in the trial.

On visiting the website participants will be asked to enter their unique identifier provided at randomisation, and to connect headphones to the computer or device they are using. Headphones will be provided if participants do not have access to their own.

First participants will complete a digits in noise test that has been widely used in a World Health Organisation hearing screening app (34). The trial version will be modified to allow the collection of ear-specific data. Data from both ears will be collected, with the contralateral ear providing a measure of test-retest variability. Next participants will complete pure tone audiometry, again collecting ear-specific thresholds.

Participants will finish the online testing by marking the severity of their dizziness and the severity of their tinnitus on a 0-10 visual analogue scale (VAS) using a slider.

It will be recommended that participants use the same location and approximate time for the hearing tests, in an attempt to improve the consistency of results and to aid in regular testing. HearX has significant experience with digital remote hearing assessment, however additional validation procedures have been included in the study analysis plan to assess if online thresholds accurately reflect in-hospital hearing test results. Online hearing tests conducted within a few days of the pre-injection pure tone audiogram tests, or the 6 and 12 week pure tone and speech tests, will be compared to the audiologist performed hearing tests.

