#### **Week 12 $\pm 7$ days after randomisation**

The following should be performed and/or collected:

- Pure tone audiogram (0.5-8.0kHz range)
- AB phoneme speech testing
- Participant complete questionnaires to include SSQ, VRBQ, TFI, HUI3, ICECAP-A.
- Resource usage
- AE monitoring (intratympanic injection arm and combination treatment arm only for persistent perforation of the tympanic membrane)

For participants who have internet access and agree to use the online digits-in-noise and pure tone tests, they will be asked to perform the tests on the trial website every week, for 12 weeks from randomisation. In rare cases where the hearing tests are unable to be performed due to an infection in either ear, the infection should be treated as per standard local protocols and the audiogram performed as soon as the infection has cleared.

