## 14.2 Analysis of outcomes

A separate Statistical Analysis Plan (SAP) will be produced and will provide a more comprehensive description of the planned statistical analyses. The reporting of the outcomes will be based on the guidelines as published in the Reporting of multi-arm parallel-group randomised trials (22). A brief outline of these analyses is given below.

The objective of the trial is to test the superiority of three interventions:

- Oral steroid
- Intratympanic steroid
- Combination oral and intratympanic steroid

All analysis will have the following two key group comparisons:

- Intratympanic steroid versus oral steroid
- Combination oral and intratympanic steroid versus oral steroid

Oral steroid group will be considered as the control group, i.e. reference category for all analyses. A comparison of intratympanic steroid versus combination oral and intratympanic steroid will also be performed as part of an exploratory analysis for all outcomes.

All primary analyses (primary and secondary outcomes including safety outcomes) will be by intention-to-treat (ITT), i.e. all participants will be analysed in the intervention group to which they were randomised irrespective of adherence to randomised intervention or other protocol deviation. As a secondary (or sensitivity) analysis, a per-protocol analysis will also be carried out for the primary outcome.

To maintain an overall 5% type I error rate, each comparison will be tested at a significance level of 2.5% to account for the increase in the risk of type I error associated with making two key comparisons. Therefore, for the primary outcome and all other secondary outcomes measures, a Bonferroni correction (23) will be applied to account for the increase in the risk of type I error associated with making two key comparisons (i.e. “intratympanic steroid versus oral steroid” and “combination oral and intratympanic steroid versus oral steroid”).

For all outcome measures, appropriate summary statistics and differences between groups, e.g. mean differences, relative risks, absolute differences will be presented, with two-sided 97.5% confidence intervals. Outcomes will be adjusted for the minimisation variables listed in section 6.4.3 and any baseline values (where applicable).

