#### 14.2.2 Secondary outcomes

The secondary outcomes consist of continuous, time to event, binary, ordered categorical with more than two categories and count data types. For all secondary outcomes that are continuous in nature, they will be analysed using the same statistical method as described for primary outcome.

Binary outcomes: For those secondary outcomes that are binary in nature, data will be summarised as number and percentage of participants in each category by intervention arm. An adjusted relative risk and 97.5% confidence interval will be estimated from a log-binomial regression model and the p-value from the associated model will be produced and used to determine statistical significance. We will also present the adjusted risk difference and the corresponding 97.5% confidence interval.

Ordered categorical outcomes with more than two categories: For those secondary outcomes that are categorical in nature with more than two categories, data will be summarised as number and percentage of participants in each category by intervention arm. An adjusted odds ratio and 97.5% confidence interval will be estimated from an ordered logistic regression model and the p-value from the associated model will be produced and used to determine statistical significance.

Time to event outcome: For those secondary outcomes that are time to event data types, these will be compared between intervention arms using survival analysis methods. Kaplan-Meier survival curves will be constructed for visual presentation of time-to-event comparisons. A Cox proportional hazards model will be fitted to obtain an adjusted hazard ratio and 97.5% confidence interval. The p-value from the associated model will be produced and used to determine statistical significance.

Count data: For those secondary outcomes that are count data type, these will be analysed using a Poisson regression model (or negative binomial regression if there is evidence of overdispersion) with an offset for the length of time the participant was in the trial included in the model, to obtain an adjusted incidence rate ratio and 97.5% confidence interval. The p-value from the associated model will be produced and used to determine statistical significance.

---

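### Time to hearing recovery exists only for participants who volunteer for home tests, so its planned Cox comparison at the 2.5% level cannot be ITT and should be labelled exploratory

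*Protocol*

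**What the plan says.** Section 8.2.2 opens with a general rule, "All secondary outcomes will be measured at 6 and 12 weeks following randomisation, except where stated", and its list includes "Time to hearing recovery: using online digits-in-noise and pure tone tests", marked optional and weekly where done. No other source is named for this outcome.

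Home testing is voluntary throughout:
- Section 5.4 makes it an optional consent statement: "Agree to use online hearing tests provided by a private company, HearX".
- Section 9, under the week 12 visit, limits it: "For participants who have internet access and agree to use the online digits-in-noise and pure tone tests".
- Section 8.3.4 says that "those who prefer not to test at home will still be able to participate in the trial".

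The analysis rules are general. Section 14.2 applies ITT to primary and secondary outcomes, so that "all participants will be analysed in the intervention group to which they were randomised", and extends the Bonferroni-corrected 2.5% level to all secondary outcomes. For time-to-event outcomes, 14.2.2 plans Kaplan-Meier curves and states: "A Cox proportional hazards model will be fitted to obtain an adjusted hazard ratio and 97.5% confidence interval". The p-value from that model is to determine statistical significance.

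Elsewhere the same data have a smaller role. The Trial Summary lists the home tests under a separate Optional heading, after the secondary outcomes. The secondary objective in 2.2 is to explore the trajectory of recovery from participant-submitted data.

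**The concern.** The protocol fixes a data source that some participants will not supply, an analysis population that includes everyone, and a model that needs a time for each person analysed. These cannot all be met. Whoever declines or cannot do home testing is absent from the risk set.

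The comparison would then no longer be protected by randomisation. Participants know their allocation (6.5), so the decision to test, and to keep testing, may depend on arm. Stopping may also be related to recovery or to the lack of it. A hazard ratio with a 97.5% interval and a significance verdict, reported under the trial's ITT statement, would look like a full-cohort result. Time to recovery is among the outcomes named in the commissioning brief, so the result is likely to be read.

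**Working it through.** **The plan's own figures.** With a difference of 10 dBHL, SD 25, two-sided alpha 0.025 and 90% power, n per arm = 2 × (2.2414 + 1.2816)² × (25/10)² = 155.1, so 156. The t-test version gives 156.4, so 157, as stated in 14.1. Then 157/0.9 = 174.4, so 175 per arm and 525 in total. SSQ power at 157 per arm is 78.5%, matching the stated figure of just under 80%. There is no arithmetic error. No event count, power or uptake is given for time to recovery, so everything numerical below rests on assumed inputs.

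**Can the rules be carried out together?**

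| Rule | Section | Participant with no home test |
|---|---|---|
| Recovery time comes from home tests | 8.2.2 | No event time, no follow-up time |
| Home tests may be declined | 5.4, 8.3.4, 9 | Stays in the trial |
| Secondary outcomes analysed by ITT at 2.5% | 14.2 | Should be analysed |
| Cox model and p-value for time-to-event data | 14.2.2 | Cannot enter the model |

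Time to hearing recovery is the only time-to-event outcome in the 8.2.2 list, so the Cox rule has nothing else to apply to.

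**Loss of precision.** For two equal arms, SE(log HR) ≈ 2/√events. Assume that half recover by week 12, within the 32–65% spontaneous recovery quoted in 1.1. Two arms of 157 then give 314 × 0.5 = 157 events.

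| Assumed uptake | Events | SE(log HR) | Interval width relative to full uptake (1/√uptake) |
|---|---|---|---|
| 100% | 157 | 0.160 | 1.0 |
| 70% | 110 | 0.191 | 1.2 |
| 50% | 79 | 0.226 | 1.4 |
| 30% | 47 | 0.291 | 1.8 |

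The width ratio depends only on uptake, not on the assumed recovery share, provided that recovery is as common in testers as in others.

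**Power, as an illustration.** Take an assumed HR of 1.5, alpha 0.025, and 2 × 175 randomised with no attrition (slightly optimistic). Power = Φ(½√events × ln 1.5 − 2.2414). Over a recovery share of 32–65%:
- full uptake: 112–228 events, power 46–79%;
- 50% uptake: 56–114 events, power 23–47%;
- 25% uptake: 28–57 events, power 12–24%.

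**Unequal testing by arm.** In a simulation with identical true recovery, home-test completion of 90% against 60% gave an HR of 0.95, and 90% against 40% gave about 0.91. That bias is modest. It does not measure bias from who volunteers, or from stopping for reasons linked to hearing; the documents give nothing from which to size those.

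**Could clinic audiograms replace the home tests?** Table 3 schedules audiograms for all arms at baseline, week 6 and week 12, and at weeks 1 and 2 for the two injection arms only. A Cox model was fitted to the first visit showing recovery, with no true difference, 32% or 65% recovered by week 12, and recovery either at a constant rate or front-loaded:
- All visits used: HR 1.02–1.09 (constant rate) and 1.03–1.26 (front-loaded). The false rejection rate reached about 18% against a nominal 2.5%, at 157 per arm.
- Weeks 6 and 12 only: HR 0.94–0.99, but recovery is located only within weeks 0–6 or 6–12.

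**The case against.** The defence has substance. The optional status is stated openly and repeatedly, and the summary and the objective describe exploration. Section 14.2 calls itself a brief outline with an SAP to follow, and 14.2.2 sets the Cox model by data type without naming this outcome. ITT as written is about analysing people in their allocated group; it does not promise complete data, and 14.2.4 drops participants with missing primary outcome data even from the primary analysis. Home tests also supply early data on the oral arm that clinic visits cannot.

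This narrows the point but does not remove it. Neither 14.2 nor 14.2.2 exempts the outcome, and 8.2.2 lists it as secondary. Dropping a few participants lost to follow-up, for whom the plan allows 10%, also differs from an outcome that by design does not exist for anyone who declines. The sensitivity analyses in 14.2.4 address the primary outcome only.

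Three stronger readings are tempting, and the documents do not support them:
- *Everyone already has clinic audiograms that could date recovery.* The shared visits place it only within a six-week interval, and adding the week 1 and 2 audiograms favours the arms that have them.
- *The plan censors people who stop testing, dates recovery at the first positive test, or ignores clinic results.* The protocol says none of this; such rules may properly sit in the SAP.
- *The trial's comparison of recovery rests on volunteers.* It does not. Extent of hearing recovery (8.2.2, Table 2) uses clinic audiometry and speech scores at 6 and 12 weeks in all arms.

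**Conclusion.** The point holds as a mismatch between the outcome's source and the inferential status given to it. Followed literally, the protocol produces a significance test at the 2.5% level in self-selected, unblinded volunteers, under a statement that all participants are analysed as randomised. The primary outcome, the sample size and the all-participant recovery comparison are unaffected.

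The size is uncertain. On assumed uptake of 30–70%, intervals are about 1.8 to 1.2 times as wide as with full uptake. Simulated bias from unequal completion alone is modest, and selection bias cannot be quantified from the documents. The case for change rests on what the trial may claim from this analysis, not on a demonstrated distortion.

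**What to change.** In 8.2.2, 14.2 and 14.2.2, label time to hearing recovery from home tests as an exploratory analysis in participants who consented to testing. Exempt it from the ITT statement and from the 2.5% significance rule. Report, by arm, how many agreed to test, how many supplied any test, and how many weekly tests were completed. This also brings 8.2.2 into line with the Trial Summary and the objective in 2.2.

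If a timing comparison in all randomised participants is wanted, base it only on the week 6 and week 12 clinic audiograms common to all arms. Classify each participant as recovered by week 6, between weeks 6 and 12, or not by week 12, using the pure tone criterion for Full Recovery in Table 2, and analyse by interval-censored or by-visit methods. Do not use the week 1 and 2 audiograms for this.

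The first change costs wording and a short uptake table, with no new data. The optional comparison costs some programming, gives only six-week resolution, and overlaps with the existing extent-of-recovery outcome, so it may reasonably be left out.

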#### **Associated Symptoms**

- **Dizziness: using the Vestibular Rehabilitation Benefit Questionnaire (VRBQ)**. This is a 22 item participant completed tool and it provides a measure of the anxiety associated with dizziness, identified as an important aspect by the ISSNHL PPI group.
- **Tinnitus: using the Tinnitus Functional Index (TFI)**. This is a 25 item participant completed questionnaire that is sensitive to changes in tinnitus severity and impact (20) and is recommended by NICE for this purpose (21).

#### **Adverse Events (AEs)**

- **Adverse events** relevant to the interventions will be recorded at 6 and 12 weeks (see section 10.3 for further details of timeline requirements of AE reporting).

#### **Health Economic Assessment**

- Two tools will be used to **assess health economics: the Health Utilities Index 3 (HUI3)**, a participant reported assessment of health-related quality of life suited to hearing loss (24,28), and **ICEpop CAPability measure for Adults (ICECAP-A)**, a participant reported measure of capability for the adult population (29).
- **Resource usage** over the past 12 weeks.

**Table 2:** The relationship between the pure tone audiogram and functional hearing assessments measured in the STARFISH trial, as well as American Academy of Otolaryngology – Head & Neck Surgery hearing recovery criteria (1).

| Degree of hearing recovery | American Academy of Otolaryngology – Head & Neck Surgery criteria / Functional change                                                                                                             | Outcome criteria                                                                                                                             |
|----------------------------|---------------------------------------------------------------------------------------------------------------------------------------------------------------------------------------------------|----------------------------------------------------------------------------------------------------------------------------------------------|
| Unchanged                  | No recovery                                                                                                                                                                                       | 
 
• <10dB change in the pure tone audiogram
 
                                               |
| Partial Recovery Unaidable | Recovery to less-than-serviceable levels indicates an ear unlikely to benefit from traditional amplification.
Can use specialist hearing aid technology but unable to restore spatial hearing. | 
 
• ≥10dB improvement in pure tone audiogram
 
• AB phoneme maximum score <50%
 
     |
| Partial Recovery Aidable   | Recovery to a serviceable level typically indicates that after recovery, the ear would be a candidate for traditional hearing amplification                                                       | 
 
• ≥10dB improvement in pure tone audiogram
 
• AB phoneme maximum score 50% or more
 
 |
| Full Recovery              | Complete recovery requires return to within 10dBHL of the unaffected ear and                                                                                                                      | 
 
• Return to normal hearing (20dB or lower) or to within 10dB of the contralateral ear
 
      |

Anticipated changes in other outcomes with unchanged hearing:

Unlikely to show a change in HUI3 score

Unlikely to show subjective changes in SSQ and other questionnaires

Anticipated changes in other outcomes partial recovery - unaidable:

Small but negligible improvements might be observed in the SSQ

Other questionnaires might indicate non speech-related improvements

Unlikely to show a change in Health Utilities Index 3 score

Anticipated changes in other outcomes partial recovery - aidable:

SSQ questionnaire will demonstrate functional improvement, which will be supported by other questionnaires

Measurable improvement in the Health Utilities Index 3 score

Anticipated changes in other outcomes with full recovery of hearing:

There will be a large change in the SSQ questionnaire and other questionnaires

Large improvements in the AB phoneme score

Large improvements in the Health Utilities Index 3 score

---

